### Economic evaluation

An economic evaluation in the form of a cost-effectiveness (CEA) and cost-utility analysis (CUA) from a societal perspective and from an employer’s perspective [36] is embedded in this trial-based economic evaluation. The time horizon and the measurement point are combined with the effectiveness study, i.e. the T0-T4 measurement. The primary outcome for the CEA is cost per continuously abstinent ex-smoker. The primary outcome of the CUA is cost per Quality Adjusted Life Year (QALYs). The utility value derived from the standard quality of life questionnaire, EuroQol 5D5L [37], using Dutch tariff [38] will be used to compute QALYs. The utilities at the various time points are used to compute QALYs by means of the area under the curve method [39].

As this economic evaluation is also performed from a societal perspective, this implies that all relevant costs and outcomes are taken into account. A separate analysis is performed from the employer’s perspective. It is hypothesized that the intervention is associated with an increased number of quitters, increase in quality of life, and decreased costs. The time horizon is 12 months. Costs (the use of resources) are measured continuously; outcomes for the economic evaluation study are measured before the start of the smoking cessation training, at 3 months, 6 months, and 12 months.

#### Cost measurement

Total costs are estimated using a bottom-up (or micro-costing) approach, where information on each element of service used is multiplied by an appropriate unit cost and summed to provide an overall total cost. Intervention costs, healthcare costs, respondent and family costs, and costs outside the health care sector are assessed, especially the cost for the employer. A cost questionnaire was especially designed for this study, based on existing questionnaires [40–43], which identifies all relevant costs aspects. Subjects are asked to report the data from their cost questionnaire relating to the previous 3 months at T0, and relating to the period in between measurements at T1-T4. The valuation of costs is based mainly on the updated Dutch manual for cost analysis [44]. Cost prices are expressed in 2017 euros. If necessary, existing cost-prices are updated to 2017 using the consumer price index.

#### Analysis of economic evaluation

The analysis of the economic evaluation contains several uncertainty analyses, including bootstrapping analysis for sample uncertainty. The results of the economic evaluation are presented in cost-effectiveness plane and cost-effectiveness acceptability curves (CEAC). The Incremental cost-effectiveness ratio (ICER) is determined on the basis of incremental costs and effects of evidence-based interventions for smoking cessation in a corporate setting compared to care as usual. The cost-effectiveness ratio is stated in terms of costs per outcome rate, the cost-utility ratio focuses on the net cost per Quality Adjusted Life Year gained.

The ICER is calculated as follows. ICER = (Ci – Cc)/(Ei – Ec), where Ci is the annual total cost of the evidence-based interventions for smoking cessation in a company setting group, Cc is the annual total cost of the care as usual group, Ei is the effects at one year follow-up for the evidence-based interventions for smoking cessation in a company setting group and Ec is the effect at one year follow-up for the care as usual group.

The robustness of the ICER is checked by non-parametric bootstrapping. Bootstrap simulations are also conducted in order to quantify the uncertainty around the ICER, yielding information about the joint distribution of cost and effect differences. The bootstrapped cost-effectiveness ratios are subsequently plotted in a cost-effectiveness plane, in which the vertical line reflects the difference in costs and the horizontal line reflects the difference in effectiveness. The choice of treatment depends on the maximum amount of money that society is prepared to pay for a gain in effectiveness, which is called the ceiling ratio. Therefore, the bootstrapped ICERs are also depicted in a cost-effectiveness acceptability curve showing the probability that evidence-based interventions for smoking cessation in a business setting is cost-effective using a range of ceiling ratios. Additionally, to demonstrate the robustness of our base-case findings, a multi-way sensitivity analysis is performed. In the sensitivity analysis, uncertain factors of assumptions in the base case analysis are recalculated in order to assess whether the assumptions have influenced the incremental cost-effectiveness ratio (ICER), for example by varying cost-prices and volumes between minimum and maximum [45].

## Discussion

This paper presents the protocol of the intervention study “Continuous Abstinence Through Corporate Healthcare” (CATCH). The aim of the study is to investigate the effectiveness of incentives on continuous abstinence in employees. A total of 516 employees, divided over 22 control and 22 intervention companies participate in a cluster-randomized controlled trial. In both groups, participants follow a seven-week smoking cessation program. In the intervention group, employees additionally receive vouchers for cessation success up to a total value of 350 euro. It is hypothesized that employees in the incentive group achieve a higher 12-month continuous abstinence rate.

### Strengths and limitations

The proposed study has several strengths, starting with its company setting. A company setting can have several advantages compared to other settings; corporations have the potential to reach a large amount of people, can motivate their employees to participate and thereby achieve high attendance rates, and may inspire peer support and positive peer pressure among colleagues [46]. Moreover, businesses have an interest in keeping their employees healthy [4].

Another strong point of this study is that the proposed study performs a cost-effectiveness and cost-utility analysis from a societal perspective and specifically from an employer’s perspective. To our best knowledge, the cost-effectiveness of financial incentives to stimulate long term smoking cessation in a company setting has not been established yet. The outcomes of the cost-effectiveness analysis can help inform employers who are considering providing smoking cessation support in combination with incentives for their employees.

What makes this study also particularly relevant is its target population of employees with a lower socioeconomic status. People with a lower education and income smoke more often [25, 47], smoke more cigarettes per day and have lower quit rates than people with a higher SES [26, 48]. Although smokers with low SES are as likely to start a quit attempt as smokers with a high SES, they are less likely to succeed in quitting smoking [49]. Potential barriers in quitting successfully are suggested to be lack of social support and financial barriers to smoking cessation treatment [47]. The current intervention aims to remove potential obstacles and to make the smoking cessation program easily accessible for employees in three ways: (1) by providing it via the employer, (2) by organizing the training sessions at the workplace, and (3) by designing the training as a group program so that colleagues can support each other both during and between sessions.

A possible limitation of this study is the lack of blinding of the research participants to the existence of the intervention and control conditions. It is expected that the incentive group is more attractive to subjects than the control group. If smokers would know for certain that the incentive is within reach, it could lead to employees signing up who only smoke occasionally and are not dependent on the training for a successful quit attempt. In contrast, the control group may appeal only to heavy smokers who are highly motivated to quit. If nothing would be arranged to avoid these potential problems, it was anticipated that the study would end up with a substantial larger number of subjects in the intervention condition than in the control condition, which could cause selection bias. To avoid this possibility, it was decided not to randomize participants prior to enrolment, but to inform them merely about their 50 % chance of being eligible to earn the vouchers. Only after enrolment, during the first training session, it is revealed whether participants are randomized into the control or intervention condition. This approach could, however, lead to attrition bias, when participants in the control group are disappointed about not being able to earn the vouchers and therefore drop out more frequently. Furthermore, it is anticipated that some larger companies will participate with more than one group. In order to avoid inequality among coworkers, it was decided that all groups within the same location of the corporation would be randomized together. A disadvantage of this decision is that when these groups do not start at the same time, it could cause selection bias, since employees in the second group of the company may find out whether they will receive the incentive or not.

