### Recruitment

In order to recruit companies, SineFuma - an organization that provides smoking cessation group training to companies - presents their clients with the possibility of participating in this research project. Additionally, the research assistant actively approaches companies by telephone and via a recruitment letter sent by post or e-mail with a visually attractive flyer attached. Press releases, media interviews and social media (Facebook, LinkedIn, Twitter) are used to create awareness of the study, and advertisements are placed in digital newsletters of several organizations, such as the Dutch Cancer Society and Lung Alliance Netherlands. Companies are targeted based on number of employees (n > 200) and socioeconomic status of employees (preferably lower educated workers).

In the recruitment process, companies are informed that they can be randomized to the incentive group or the control group. To which group the company is assigned is revealed during the first session of the smoking cessation training. This means that a company needs to decide to participate in the research without knowing the final result of the randomization.

When a company decides to participate in the study, participants within the company are recruited using advertisements via the corporate website, email, posters and informative flyers that are spread through the company building. On these promotion materials it is advertised that participants have a chance to earn financial incentives with a total amount of 350 euro. On request of the company, SineFuma or the research assistant organizes an informal presentation at the company to inform employees who consider participating in the training. Prior to enrolling in the study, employees receive an information letter and are asked to give their signed informed consent. In this information letter, the chance of being eligible to earn the financial incentives is explained, and detailed information on the smoking cessation training and the research procedures is provided.

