### Randomization

Participants are allocated via cluster-randomization on a company level to the intervention or control group. For large corporations with several branches in which the participants are not in direct contact with each other, each location is entered separately in the randomization. The randomization procedure is performed by an independent research assistant. The sequence of the randomization is generated with a digital randomization program using the biased urn method [33, 34], where the proportion of being randomized into a group is inversely related with the proportion of participants who are already randomised into that group, in order to maintain treatment balance throughout the trial.

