### Statistical analysis

Based on the intention-to-treat principle, all randomized participants are included in the denominator for calculating abstinence rates with the exception of unavoidable loss to follow-up as stated the Russel Standard [29]. The primary effectiveness analysis examines the difference in prolonged smoking abstinence between intervention group and control group over a period of twelve months after the counseling sessions. To be able to account for repeated measures and nesting of participants within companies, generalized mixed models with the logit link are used. Time, group (intervention or control) and the interaction between time and group are entered in the model as fixed factors. Baseline measurements such as socioeconomic status (based on income and education) and nicotine dependence are considered as potential effect modifiers, and will therefore be explored by moderation in the analysis. If those are indeed effect-modifiers, the effects for each level of socioeconomic status and nicotine dependence are reported. In case of missing values in these potential effect modifiers, multiple imputation approach is used. Missing data in the outcome variable are not being imputed, since the likelihood-based approach is used to deal with missing values [35]. A two-tailed test is considered statistically significant with p-values <0.05.

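### Where training groups at one location start at different times, later enrolees may already know their arm; the protocol names this selection bias but states no countermeasure

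*Protocol article*

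**What the plan says.** The unit of allocation is the company, or the separate branch of a large corporation: "Participants are allocated via cluster-randomization on a company level to the intervention or control group" (Protocol article, Randomization).

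Concealment rests on timing. Under Recruitment, "To which group the company is assigned is revealed during the first session of the smoking cessation training". Strengths and limitations gives the reason: to prevent selective sign-up, "it was decided not to randomize participants prior to enrolment", and people are told only that they have an even chance of the vouchers. "Only after enrolment, during the first training session, it is revealed whether participants are randomized into the control or intervention condition".

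The same section then describes multi-group sites. First, "it is anticipated that some larger companies will participate with more than one group". Second, to treat coworkers alike, "it was decided that all groups within the same location of the corporation would be randomized together". It accepts that, if those groups do not start together, selection bias could follow because "employees in the second group of the company may find out whether they will receive the incentive or not". The discussion of the problem ends there.

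Under Statistical analysis, "all randomized participants are included in the denominator for calculating abstinence rates", apart from unavoidable loss to follow-up. The fixed factors are time, arm and their interaction, with nesting in companies. Nicotine dependence and socioeconomic status enter as possible effect modifiers.

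**The concern.** Concealment until after enrolment is the only stated protection against differential enrolment, and it works for a person only if that person enrols before the location's allocation is disclosed. Disclosure happens at a first training session. At a location with staggered groups, the first group's first session makes the allocation available to colleagues who have not yet signed up. Their chance of the vouchers is then no longer even, and they may know it.

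The protocol states what it expects when smokers know the incentive is available: occasional smokers, who would not need the course to quit, may sign up. Eligibility (Study population) requires current smoking and adult age but no minimum consumption or dependence, so such people would qualify. If they join later groups at incentive locations, 12-month abstinence in that arm rises whether or not the vouchers work. Exploring dependence as a moderator does not remove this from the overall arm contrast.

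**Working it through.** **1. The plan's own sample size.** Inputs from Sample size calculation: 15% vs 5%, alpha 0.05, 80% power, m = 12, ICC 0.05, 15% loss. The two-sided test is stated in Statistical analysis.

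- n = [1.96·√(2·0.10·0.90) + 0.8416·√(0.15·0.85 + 0.05·0.95)]² / 0.10² = 140.1, so 141 per arm.
- Design effect = 1 + 11·0.05 = 1.55; 141 × 1.55 = 218.55, so 219 per arm.
- 2 × 219 / 0.85 = 515.3, so 516 in total.

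The stated figures reproduce. There is no arithmetic error here; the point concerns recruitment timing.

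**2. How many people could be in later groups.** The documents do not say. The planned mean is 516/44 = 11.7 per company, and training groups hold about 8 to 16 (Smoking cessation counseling). With average group size g, the number of groups is 516/g, and those beyond one per company are 516/g − 44:

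- g = 8: 64.5 groups, 20.5 extra, share 20.5 × 8/516 = 32% of participants.
- g = 10: 51.6 groups, 7.6 extra, share 7.6 × 10/516 = 15%.
- g = 12: 43 groups, none extra.

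These shares count everyone in an additional group, assuming 44 locations and later groups of average size. The share that enrols after disclosure is smaller if some groups run concurrently or some members consent early.

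**3. Size of a spurious difference (illustration).** Assume no true effect, a share f of each arm in post-disclosure groups, and selection raising abstinence by s in later incentive groups only. Neither f nor s is in the documents.

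Spurious difference = f × s. For f = 20%: 0.20 × 0.10 = 2.0 points and 0.20 × 0.14 = 2.8 points.

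The rejection rates below use a two-proportion normal approximation with effective n = 219/1.55 = 141 per arm and s = 10 points, for common base rates of 5% and 15%. The nominal rate is 5%.

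| Share f | s = 10 points | s = 14 points | Rejection, base 5% | Rejection, base 15% |
|---|---|---|---|---|
| 10% | 1.0 | 1.4 | 6.6% | 5.6% |
| 20% | 2.0 | 2.8 | 10.9% | 7.4% |
| 32% | 3.2 | 4.5 | 19.1% | 11.1% |

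**4. Cost of restricting to pre-disclosure enrolees.** Per-arm n = 219(1 − f), cluster size = 12(1 − f), design effect recomputed, planned rates 15% vs 5%:

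- f = 10%: n = 197.1, design effect 1.49, power 77.7%.
- f = 20%: n = 175.2, design effect 1.43, power 74.5%.
- f = 32%: n = 148.9, design effect 1.358, power 69.7%.

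Without restriction it is 80.3%.

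**The case against.** The authors disclose this limitation themselves and give a reason for accepting it: fairness among coworkers. Nothing in the article is misstated. That stands, but naming a bias does not control it, and fairness requires one allocation per location, not enrolment after disclosure.

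A sensitivity analysis by enrolment timing could sit in an SAP that is not shown. This also stands, so its absence from the article is not counted as a fault in itself. The recruitment gap is different: an analysis plan cannot restore concealment once it is lost. T0 does record nicotine dependence and pack-years (Questionnaires), so imbalance could be examined, but the article plans to use dependence only for moderation.

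A reader might infer that every later group enrols knowing its arm. The text does not support that. It is conditional twice: groups must start at different times, and employees may, not will, find out. Concurrent groups are unaffected, as are members of a later group who consented before the first group's session. Nor does recruiting companies with more than 200 employees show that multi-group sites are common, since the planned mean is about one group per company.

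A reader might also infer that selection lowers abstinence in later control groups and so widens the bias. The protocol expects known control status to appeal to heavy smokers with strong motivation to quit. Those two traits may pull abstinence in opposite directions, so the illustration leaves the control arm unchanged.

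Finally, a stricter remedy, with T0 taken early for all groups and every late sign-up excluded, has real costs. It would lengthen the T0 to T1 interval used for costs and QALYs. At shares of 10% to 30% it could also remove about 52 to 155 of the 516 participants, unless most could be enrolled early. That objection is accepted in the fix.

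**Conclusion.** The concern holds in a conditional form. At locations with staggered training groups, people who enrol after the first group's first session may know their allocation. The concealment safeguard can then fail for them, the article states no countermeasure, and the primary model pools them with concealed enrolees. Followed as written, the plan can bias the primary contrast.

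The size cannot be derived from the documents. It is probably confined to some larger companies. The 2.0 to 2.8 points at a 20% share, against a planned difference of 15% − 5% = 10 points, are illustrative. They assume equal later-group shares in both arms, a 10- to 14-point lift in later incentive groups and no shift in later control groups. With no later enrolees the bias is zero. The point merits action because the remedy is cheap, not because a large bias has been shown.

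**What to change.** - Record each participant's consent date and the date on which allocation was disclosed at that location.
- Pre-specify, if the SAP does not already do so, a sensitivity analysis of the primary endpoint restricted to participants who consented before their location's disclosure date. Define membership by consent date, not by attendance.
- Compare baseline nicotine dependence by arm, separately for pre- and post-disclosure enrolees.
- Where several groups at a location are already planned, take signed consent for all of them before the location's first session if feasible. Keep T0 at its usual time before each group's own training.

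The cost is a little extra record keeping and lower precision in the restricted analysis: power of roughly 70% to 78% instead of 80% for shares of 32% down to 10%. Early consent has one side effect to watch. Later-group controls may learn their arm before their training starts, which could add to the disappointed drop-out that the protocol already anticipates. Late sign-ups need not be excluded from the trial; they stay in the primary analysis and are identifiable.

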## Conclusion

The proposed study is the first in the Netherlands that investigates the effect of financial rewards on smoking cessation and the first study worldwide that assesses the cost-effectiveness of incentives to decrease smoking in employees. The results of this study can provide important recommendations for the use of financial incentives to motivate employees to quit smoking.

## Abbreviations

CATCH: Continuous Abstinence Through Corporate Healthcare; title of the project
Cc: The annual total cost of the care as usual group
CEAC: Cost-effectiveness acceptability curves
Ci: Annual total cost of the evidence-based interventions for smoking cessation in a company setting group
CO: Carbon monoxide
COPD: Chronic obstructive pulmonary disease
Ec: The effect at one year follow-up for the care as usual group
Ei: The effects at one year follow-up for the evidence-based interventions for smoking cessation in a company setting group
ICER: Incremental cost-effectiveness ratio
